### Data collection, management, and monitoring

Before the start of the trial, all investigators from each site have been trained in the clinical trial protocol, data management, and methodology of indicator evaluation. Electronic case report form (CRF) was designed by the statistician according to the trial protocol and medical record. Participant log was distributed to each patient to record their daily use of OK lens and eyedrops. During the study, investigators collected the data and recorded it on the participant medical record.

In the present study, the main adverse events were mainly conjunctivitis or keratitis after wearing OK lens and sensitivity to light or ocular irritation after instillation of eyedrops. The masked investigators examined cornea and conjunctiva using the slip-lamp microscopy at each visit time. Once the presence of any abnormal ocular symptoms occurs, the nightly wear of the OK lens and use of the atropine or placebo eyedrop would both be suspended. And at least one masked investigator would review and report the signs and symptoms in a timely manner according to the procedures. Each adverse event would be recorded in the CRF. Participants who are unable to be followed up throughout the study are considered dropout of our study. Once the intolerable side effects occur or the effect of treatment is poor, the participants could withdraw from the study. Additionally, participants could withdraw from the study for any reason at any time. The investigators may also withdraw participants from the study to protect their safety.

To ensure the quality of the clinical trial, an independent committee, including statisticians, ophthalmologist, and members of the ethics committee of Shanghai General Hospital, was established and oversaw the study throughout the study period. They monitored the progress and safety of the study and reported their recommendation to the principal investigator. This committee was independent from the trial researchers. Participant medical records were stored securely in locked cabinets in the research laboratory at each site. Only the investigators and monitors have access to participant medical records. The data and information of the participants would not be used in other ancillary studies. In order to protect the privacy of the participants during data analysis, their identity information was hidden. There was no interim analysis and no stopping rules in this study. Auditing was performed by Good Clinical Practice (GCP) office of Shanghai General Hospital. They reviewed the progress of the trial every six months. The process was independent of investigators.

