### Sample size calculation

The two-sample *t* test for superior statistical analysis was used for the sample size calculation. The parameters used for the sample size calculation included the following: a significance level of 0.05, 95% confidence interval, 80% power, and 1:1 allocation. According to previously published articles, the axial length elongation in the combination of OK lens and 0.01% atropine group was preset at 0.09 ± 0.12 mm, while the OK lens was preset at 0.19 ± 0.15 mm in 1 year [24]. According to the previous experience of the investigators with clinical trials for treating myopia and other published data, the rate of participant loss to follow-up over 2 years was estimated to be 20%. Calculations, which were two-sided, were performed using the software, NCSS PASS 11. A total sample of 96 eligible children was required in the trial, with 32 participants being planned to be assigned to each of the three study sites.

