## Trial status

At the time of submission, recruitment has already ended, and all the participants were under follow-up visits. The recruitment date of the first patient is 25 January 2019. The date of recruitment of the last patient is 13 July 2020. A total of 96 children were recruited. The 24-month visit is expected to be completed on 17 August 2022. The work was delayed due to the coronavirus pandemic. The protocol version is 1.0, dated 20 April 2018.

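### Poor treatment effect is a named ground for leaving the study, with no 24-month axial length provided for afterwards, so primary-outcome values may go missing in relation to progression

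*Protocol article*

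**What the plan says.** All references are to the Protocol article.

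- **Withdrawal** (Data collection, management, and monitoring): "Once the intolerable side effects occur or the effect of treatment is poor, the participants could withdraw from the study". The next sentence separately gives the general right to leave at any time without a particular reason.
- **Dropout** (same section): "Participants who are unable to be followed up throughout the study are considered dropout of our study". This is defined by follow-up, not by treatment.
- **Suspension** (same section, and Intervention): lens wear and drops are both suspended when abnormal ocular symptoms appear. No exit from the study is attached to that rule.
- **Primary outcome**: change in axial length from baseline to the 24-month visit.
- **Statistics analysis**: the full analysis set (FAS) needs at least one use of the drops and an efficacy evaluation. Missing values are not imputed in the primary analysis, and multiple imputation is a sensitivity analysis. The per protocol set (PPS) keeps only children on schedule for two years.
- **Sample size calculation**: "the rate of participant loss to follow-up over 2 years was estimated to be 20" per cent.
- **Trial status**: "recruitment has already ended, and all the participants were under follow-up visits".

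**The concern.** The outcome is axial elongation, and a child in whom treatment works poorly is a child whose eye is growing fast. Naming poor effect as a reason to leave the study ties the chance of a missing 24-month value to the quantity being measured. The article has wording for stopping treatment alone (the suspension rule), but for poor effect and intolerable side effects it speaks of leaving the study.

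A child who leaves without a 24-month length contributes nothing to an unimputed comparison of 24-month change. If fast progressors leave more often, the comparison is among children who did acceptably well. More of them would be expected to leave the arm with faster growth, so the observed difference would be too small and power would fall. The PPS analysis does not guard against this, because it selects further on adherence. A separate analysis plan could change the modelling, but it could not recover lengths that were never measured.

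**Working it through.** **1. The plan's own figure.** Inputs from Sample size calculation: "a significance level of 0.05, 95% confidence interval, 80% power, and 1:1 allocation"; "Calculations, which were two-sided, were performed using the software, NCSS PASS 11"; "atropine group was preset at 0.09 ± 0.12 mm, while the OK lens was preset at 0.19 ± 0.15 mm in 1 year"; 20% loss; "A total sample of 96 eligible children was required in the trial".

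n per arm = 2·SD²·(1.960 + 0.842)² / 0.10², then divided by 0.80 for loss.

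- With both stated SDs, SD = √((0.12² + 0.15²)/2) = 0.136. This gives n = 29, or 31 by the Welch t test. 31/0.80 → 39 per arm, 78 in total.
- With SD 0.15 in both arms, n = 36, or 37 by the t test. 37/0.80 → 47 per arm, 94 in total. The next multiple of 12 (three sites, blocks of four) is 96.

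So 96 is reproduced to within two children, but only with a common SD of 0.15, which the text does not state. The check below uses both stated SDs.

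**2. Reference case: 20% lost at random.** 48 × 0.80 = 38.4 per arm. SE = √((0.12² + 0.15²)/38.4) = 0.0310. Power = Φ(0.10/0.0310 − 1.96) = 90%. The t test with 38 per arm gives 89%.

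**3. Exit related to elongation.** Assumptions, none of them given in the documents: normal outcomes with the 1-year planning means and SDs; completers only; the same rule in both arms, logit P(leave | y) = a + b(y − 0.14). The slope is b = ln 2/0.14 or ln 3/0.14, so the odds of leaving double or triple per 0.14 mm, a step close to the SD of 0.136. The constant a is set to give the stated overall loss. Completer means and SDs come from numerical integration over each arm's distribution. Power is Φ(difference/SE − 1.96), with SE from the completer SDs and numbers, starting from 48 per arm.

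| Overall loss | Odds per 0.14 mm | Loss, combination / OK lens | Completer means (mm) | Difference (mm) | Shrinkage | Power |
|---|---|---|---|---|---|---|
| 20% | ×1 | 20% / 20% | 0.0900 / 0.1900 | 0.100 | 0% | 90% |
| 20% | ×2 | 16% / 24% | 0.0791 / 0.1656 | 0.086 | 14% | 82% |
| 20% | ×3 | 14% / 26% | 0.0758 / 0.1528 | 0.077 | 23% | 75% |
| 10% | ×2 | 8% / 12% | 0.0847 / 0.1770 | 0.092 | 8% | 90% |
| 10% | ×3 | 6% / 14% | 0.0833 / 0.1694 | 0.086 | 14% | 87% |

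Differences are taken before rounding. For the row with 20% loss and ×2: completer SDs 0.1175 and 0.1439, numbers 40.3 and 36.5, SE = √(0.1175²/40.3 + 0.1439²/36.5) = 0.0302, and 0.0864/0.0302 − 1.96 = 0.90, so Φ = 82%. With 10% lost at random, power would be 93%.

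**4. Bounds.** If the fastest 20% overall left without exception, the observed difference would be about 0.040 mm and simulated power about 38%. If fast progressors left only the combination arm (10% or 20% of it), the difference would be overstated at about 0.124 or 0.142 mm.

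**5. What retention could return.** With 24-month values from all 48 per arm, power on the stated inputs is 94.6%, against 88.6% with 38 per arm (t test). This is an upper bound, because values measured off treatment may dilute the 0.10 mm.

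**The case against.** The strongest reply is that the sentence grants a permission. Children may leave for any reason anyway, so naming two reasons opens no exit that was closed. Dropout is defined by follow-up, the suspension rule carries no exit, and the FAS does not require continued treatment, so a child who stops treatment but is still measured already counts. The full protocol (version 1.0) is not shown and may arrange follow-up after treatment stops.

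Much of this stands. A reader might infer that poor responders are removed and their measurement ends; the wording is permissive and does not say so. What remains is that the article links poor effect to leaving the study and nowhere offers stopping treatment while staying in follow-up. That goes beyond silence, though the full protocol could soften it.

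A reader might also infer that side effects drive children out of the atropine arm in particular. The documents do not support this: the Background describes side-effects of 0.01% atropine as negligible, no rates by arm are given, and both arms wear the lens that is linked to conjunctivitis and keratitis. The argument rests on poor effect.

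Nor is it right that the loss is beyond repair. Visits at 1, 6, 12 and 18 months precede the endpoint. Where exit follows progression recorded there, the data are close to missing at random and multiple imputation can use those values. That repair sits only in a sensitivity analysis, and it does not reach exit that depends on unrecorded progression.

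Finally, the 20% is a general loss estimate with no reasons given. Treating all of it as outcome-related is the unfavourable case, which is why 10% is also shown.

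**Conclusion.** The point holds as a weakness of design with a bounded effect: the plan permits primary-outcome loss that depends on progression, and the primary analysis does nothing about it. On the planning inputs, with a common exit rule and odds of leaving doubled to tripled per 0.14 mm, the 0.10 mm difference becomes 0.086–0.077 mm (14–23% smaller) if all of the 20% loss is outcome-related, with power of 82–75% instead of about 90%. At 10% loss the shrinkage is 8–14%.

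Under a common rule the bias is towards no effect, so it costs power and does not create false superiority. Overstatement requires exit that differs by arm, for which the documents give no evidence. The sizes rest on an assumed exit mechanism and on 1-year means and SDs applied to a 24-month endpoint; the documents give no 2-year SDs. It should be corrected, because the remedy is cheap and missing lengths cannot be reconstructed later.

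**What to change.** Amend the follow-up procedure so that stopping treatment and ending follow-up are separate events, recorded separately with reasons:

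- Children who stop drops or lens for any reason stay in the remaining scheduled visits.
- The 24-month axial length is sought from every randomized child whose family has not withdrawn consent to follow-up, including children who have already left but whose visit is still due.
- These values are analysed in the FAS in the randomized arm.

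The rules for suspending or stopping treatment, and the right to withdraw, are left as they are. Because study procedures change, the Protocol amendments section calls for a formal amendment approved by the institutional review board; a memorandum is not enough.

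Cost: the amendment, a reminder to three sites, renewed contact with some families, and attendance at visits already in the schedule. Some values will be measured off treatment and may dilute the difference, so the result describes the effect of assignment. Visits already missed cannot be recovered. Trial status dates the last recruitment to 13 July 2020 and expects the 24-month visits to finish on 17 August 2022, so at publication (1 December 2021) the fix could help only children recruited from about December 2019 onwards.

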### Statistics analysis

The patients who took eyedrops at least once after randomization and have corresponding efficacy evaluation were analyzed as the full analysis set (FAS). In the primary analysis, missing values in FAS will not be imputed, but multiple imputation will be used to deal with missing data in sensitivity analysis. Robustness of the results will be evaluated through sensitivity analysis in the per protocol set (PPS). And the PPS refers to subjects who were able to wear OK lens and eyedrops on schedule for 2 years. Patients who received study treatment at least once with safety assessment during the trial were analyzed as safety set (SS). The primary outcome was analyzed in the FAS and PPS, and secondary outcomes were analyzed only in the FAS. The safety was evaluated in the SS.

Continuous data were presented as the mean ± standard deviation (SD) or medium (P25-P75), while categorical data were presented as numbers (percentages). For the primary outcome, ANCOVA model with center effect correction was used to compare the difference of change from baseline between two groups and calculated its 95% CI. For the secondary efficacy outcomes, ANCOVA models were used to compare the difference of change from baseline between two groups. The distribution of adverse events of the two groups is described, and chi-square test or Fisher’s exact probability test was employed for comparison of incidence between the two groups. There was no predefined subgroup analysis in this study. All statistical analyses were performed with SAS software (version 9.4), and statistical significance was set as *P* < 0.05 with a two-sided test unless otherwise noted.

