The exact mechanism of the myopia control of OK lens or atropine eyedrop is presently not fully understood. Recently, OK lens is known to control myopia progression by reducing the peripheral hyperopic defocus [18]. Atropine is thought to have effects on anti-muscarinic receptors of the retina and sclera [19]. Chen et al. reported that large pupil diameters can facilitate the effect of OK lens to slow axial growth in myopia [20]. In addition, 0.01% atropine eyedrop were proven to have a significant increase in pupil size [21]. Thus, the combination of OK lens and 0.01% atropine treatment may have great potential in magnifying the effectiveness of myopia control. In a previous randomized clinical trial conducted in Japan, the combination therapy was more effective in slowing axial elongation than monotherapy of OK lens over the 2 years (0.29 mm vs. 0.40 mm) [22]. Pauline and his colleagues set a randomized, observer-masked, prospective study in Hong Kong [23]. They found the additional use of 0.01% atropine did not affect the OK lens performance or clinical responses after 1 month of treatment [23]. The possible synergistic effect of combination treatment for myopia control needs longer study duration. However, these studies were not masked to the participants, and the control group only receives OK lens treatment without placebo eyedrop. Thus, we conducted a randomized, controlled, double-blind and multicenter trial to investigate the additive effects of the combination of OK lens and 0.01% atropine eyedrop in slowing axial elongation in children with myopia.

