### Intervention

Eligible participants were randomly assigned to the combination of OK lens and 0.01% atropine group, or the combination of OK lens and placebo eyedrop group, at a 1:1 ratio. Participants were recruited from 3 hospitals in China. To ensure balance in study site, a stratified and block randomization algorithm was used and randomization was stratified by study site and block sizes of four were used within each strata. The 0.01% atropine and placebo eyedrop looked identical in the appearance and was labeled according to the randomization code number. The participants got the eyedrop that corresponded to the assigned consecutive number in accordance with their entrance to the study.

The treatment for the combination of OK lens and 0.01% atropine group comprised of the instillation of one drop of 0.01% atropine in each eye, at 10 min before OK lens insertion, and at least 8 h of overnight wear of OK lens. Participants in the OK lens group wore the OK lens every night after the placebo eyedrop instillation. Under the condition of illness or the presence of any abnormal ocular symptoms, the nightly wear of the OK lens and use of the atropine or placebo eyedrop would both be suspended. Follow-up visits were performed at 1, 6, 12, 18, and 24 months from randomization. We provided the 3-month dosage of 0.01% atropine eyedrop or placebo eyedrop at a time. The parents or guardians are required to return the consumed vials to the investigator every 3 months. The eyedrops were being sent to minimize dropouts during the pandemics.

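### If treatment works and some children leave because of fast eye growth, the observed-only 24-month primary analysis probably understates the benefit

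*Protocol article*

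**What the plan says.** Under Primary outcome, the Protocol article takes the change in axial length from baseline to the 24-month visit as the endpoint. Under Statistics analysis it compares the arms by ANCOVA with correction for centre, in a full analysis set (FAS) limited to treated children who have an efficacy evaluation. On missing data it says: "In the primary analysis, missing values in FAS will not be imputed, but multiple imputation will be used to deal with missing data". The sentence goes on to place the multiple imputation in a sensitivity analysis. The other robustness check is the per protocol set (PPS), made up of children who kept to lens and drops for 2 years.

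Under Data collection, management, and monitoring: "Once the intolerable side effects occur or the effect of treatment is poor, the participants could withdraw from the study". Under Sample size calculation, "the rate of participant loss to follow-up over 2 years was estimated to be 20" percent. Under Intervention: "Follow-up visits were performed at 1, 6, 12, 18, and 24 months from randomization". Axial elongation at 1 year is a named secondary outcome.

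**The concern.** A single-time-point ANCOVA without imputation gives no weight to a child who has no 24-month value, whatever was measured earlier. Poor effect in this trial means fast growth, which is the primary outcome itself. If atropine adds benefit, more children on lens plus placebo meet that description. The control children who remain are then a slower-growing selection, and the difference between the arms shrinks.

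The earlier axial lengths, on which a withdrawal for poor effect would rest, do not enter the primary estimate. When dropout depends on them, the observed-only contrast is biased even under missing-at-random. At stake are a diluted estimate and lost power in a trial designed around a difference of 0.10 mm.

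**Working it through.** **Planned loss.** 0.20 × 96 = 19.2, so about 19 children without a primary value and 96 × 0.80 / 2 = 38.4 per arm with one.

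**Inputs from the documents.** For 2 years, Background reports that "the combination therapy was more effective in slowing axial elongation than monotherapy of OK lens over the 2 years (0.29 mm vs. 0.40 mm"), a difference of 0.11 mm. For 1 year, Sample size calculation says that the combination "was preset at 0.09 ± 0.12 mm, while the OK lens was preset at 0.19 ± 0.15 mm in 1 year", a difference of 0.10 mm.

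**Assumptions not in the documents.** The 24-month SD is 0.22 mm. There is 8% random loss in each arm. A child whose 12-month growth exceeds 0.25 mm withdraws with probability p = 0.2 to 0.5, under the same rule in both arms. Growth is the sum of four normal half-year increments with common correlation ρ = 0.3 or 0.6.

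**Formulas.**
- SD of 12-month growth: s = 0.22 × √[(2+2ρ)/(4+12ρ)], which is 0.129 (ρ = 0.3) or 0.118 (ρ = 0.6).
- Slope of 24-month on 12-month growth: b = (1+3ρ)/(1+ρ), which is 1.46 or 1.75.
- With 12-month mean m and z = (0.25 − m)/s, the observed 24-month mean falls by b × p × s × φ(z) / [1 − p × Q(z)]. Here φ is the normal density and Q the upper tail. Random loss does not move the mean.

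**One case in full** (even growth, so 12-month means of 0.29/2 = 0.145 and 0.40/2 = 0.20; ρ = 0.6, p = 0.5):
- Combination: z = 0.893, φ = 0.2678, Q = 0.186. Fall = 1.75 × 0.5 × 0.1176 × 0.2678 / (1 − 0.093) = 0.0304.
- Control: z = 0.425, φ = 0.3645, Q = 0.3353. Fall = 1.75 × 0.5 × 0.1176 × 0.3645 / (1 − 0.1677) = 0.0451.
- Observed difference: 0.11 − (0.0451 − 0.0304) = 0.0953 mm, which is 13.3% too small.

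**Range** (observed-only difference in mm, with attenuation from 0.11):

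| 12-month means | ρ | p = 0.2 | p = 0.3 | p = 0.4 | p = 0.5 |
|---|---|---|---|---|---|
| Even: 0.145 vs 0.20 | 0.3 | 0.1063 (3.4%) | 0.1039 (5.6%) | 0.1011 (8.1%) | 0.0979 (11.0%) |
| Even: 0.145 vs 0.20 | 0.6 | 0.1054 (4.2%) | 0.1025 (6.8%) | 0.0992 (9.9%) | 0.0953 (13.3%) |
| Year-1 benefit: 0.09 vs 0.19 | 0.3 | 0.1027 (6.6%) | 0.0984 (10.6%) | 0.0936 (14.9%) | 0.0882 (19.8%) |
| Year-1 benefit: 0.09 vs 0.19 | 0.6 | 0.1013 (7.9%) | 0.0962 (12.5%) | 0.0906 (17.6%) | 0.0845 (23.2%) |

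At p = 0.4 to 0.5, total loss is about 15 to 18% (combination) against 20 to 24% (control) with even growth, and 11 to 13% against 19 to 23% with year-1 benefit. A simulation of the p = 0.5, ρ = 0.6 cases gave 0.096 and 0.085 mm for observed values only. Filling missing values by arm from the 12-month change gave 0.110 mm in both.

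**A second set-up** fixes loss at 20% and varies the share due to poor effect (correlation of 12- with 24-month change assumed 0.8):
- True difference 0.11 mm, SD 0.20 assumed, dropout driven by 12-month growth: 0.095, 0.086 and 0.074 mm when the share is a quarter, a half and all. A half means (0.11 − 0.086)/0.11 = 22% too small.
- True difference 0.10 mm, with the 1-year means and SDs used as if they were 24-month values: 0.080, 0.067 and 0.052 mm. A half means 33% too small. Filling from the 12-month value returns 0.100.
- The same, but dropout driven by the 24-month value itself: 0.075, 0.059 and 0.040 mm. Filling recovers only part (0.089, 0.079, 0.065).
- No loss due to poor effect, or no true effect: bias about zero.

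**The case against.** Three arguments stand. First, multiple imputation is planned. If its model includes the earlier visits, it makes essentially the same missing-at-random correction as a repeated-measures model, so such handling is not absent. The model's content may properly sit in an analysis plan that is not shown. Second, the withdrawal sentence is a permission with no stated frequency, and some losses may be unrelated to growth: drops were sent out to limit dropout during the pandemic. Third, the 0.25 mm threshold is severe. Background's spectacle wearers grew 0.61 to 0.70 mm in 2 years, about 0.31 to 0.35 mm a year, so 0.25 mm is a low bar for poor effect. The largest shift in the table, 0.0255 mm, is about half a standard error (0.22 × √(2/38.4) = 0.050 mm).

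What remains is that the imputed result sets neither the primary estimate nor its P value, and the PPS repeats the selection. A systematic shift smaller than the sampling error still costs power.

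A reader might infer that the primary estimate is certainly biased, or by a quarter or more. The documents support neither: bias needs a non-zero effect and growth-driven withdrawals, and the larger figures need nearly all benefit in year 1 or a large share of loss due to poor effect. A reader might also infer that withdrawal for side effects could inflate the benefit. That would require those leavers to differ in growth. No figure supports it, and Background calls side effects at this concentration negligible.

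**Conclusion.** The concern holds in conditional form. The text fixes an observed-only primary contrast and itself names an outcome-related reason for leaving. If the combination works and some children leave because of fast growth, the primary difference is probably too small. Under the assumptions above, the shortfall is about 4 to 13% with even growth and about 7 to 23% when most benefit arises in year 1. It is larger if poor effect causes half or more of a 20% loss. The direction is dilution and loss of power; with equal withdrawal rules and no true effect, no false benefit arises. Using the 12-month value restores the true difference when dropout depends on that value, and only part of it when dropout depends on unseen later growth.

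The stated sample-size inputs do not reproduce 96: a two-sided t test with unequal SDs needs 31 per arm, and 31/0.8 rounds up to 39, or 78 in total. That is a separate matter and does not affect this point.

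**What to change.** Before unblinding, make the primary analysis one that is valid under missing-at-random and uses the earlier axial lengths. There are two routes:

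- A repeated-measures model of axial-length change with arm × visit, baseline axial length × visit, centre and unstructured covariance, and the 24-month contrast as primary. It should cover the visits at which axial length is measured. The text confirms 12 and 24 months; the schedule table is not shown, so 1, 6 and 18 months need checking.
- The multiple imputation already planned, promoted to primary, with the earlier visits in the imputation model.

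Keep the observed-only ANCOVA as a sensitivity analysis.

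The cost is a change of analysis wording and a slightly more complex primary model that relies on missing-at-random. It needs no new data. The article reports children still in follow-up at submission and no interim analysis, so there was room to make the change blind. Continued measurement of children who stop treatment would reduce missing data at source. That is a change of study procedure, which under Protocol amendments needs a formal amendment and review board approval, so it should be considered separately.

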## Background

The prevalence of myopia is dramatically increasing, worldwide, especially in East Asia [1]. Recent studies have indicated that the prevalence of myopia in East Asian countries has reached as high as 90% [2]. It is estimated that there will be approximately five billion people (half of the world’s population) with myopia by 2050 [1]. In addition, myopia occurs at younger ages. A number of studies have presented that children who develop myopia at a younger age is prone to progress more quickly and ultimately progress to high myopia [3, 4]. Myopia progression is usually accompanied by the elongation of the axial length, which may result in vision-threatening pathology, such as macular degeneration, retinal detachment, and glaucoma [5, 6]. Given the high prevalence of myopia and its strong association with sight-threatening ocular diseases, myopia has become a major public health concern. Hence, it is critical to explore effective strategies to control myopia progression.

At present, numerous studies have assessed the efficacy of OK lens and atropine for myopia control in children [7–9]. OK lens was originally designed to correct myopia and provide clear unaided visual acuity during the day. At present, increasing evidence has shown that OK lens is effective for slowing axial elongation and myopia progression. A single-masked randomized clinical trial conducted in Hong Kong revealed that the increase in axial length in the OK lens group was less than that in the single-vision spectacle glasses group (0.36 mm vs. 0.63 mm) at 2 years [7]. In the cohort study conducted in Japan, the increase in axial length for over 2 years was 0.39 mm and 0.61 mm in the OK lens and the single-vision spectacle glasses groups, respectively [8]. In a retrospective cohort study conducted in China, the OK lens group exhibited less changes in axial length, when compared to the single-vision spectacle glasses group, at 2 years (0.34 mm vs. 0.70 mm) [9]. In conclusion, OK lens can induce a 40–60% mean reduction in axial elongation, when compared to single-vision spectacles, in terms of correcting myopia, at present.

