### Participant eligibility

#### Inclusion criteria

The participants were within 8–12 years old. These participants intended to undergo the OK lens treatment. The inclusion criteria for the present study were as follows: spherical equivalent refractive error between − 1.00 and − 4.00 D in either eye, astigmatism of no more than 1.50 D in either eye, a best corrected visual acuity (BCVA) of no worse than 25/25 in both eyes, the weight of birth was no less than 1500 g, the patient/guardian agrees to be randomized, and attends the scheduled and follow-up visits.

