### Randomization and masking

A statistician was responsible for the randomization of the 0.01% atropine eyedrop or placebo eyedrop, which was achieved using a web-based randomization program. The randomization was stratified by center with fixed block size of 4. Cards that identified the combination of OK lens and 0.01% atropine group and OK lens group were placed in sealed opaque envelopes and kept by the principal investigator until the conclusion of the trial. The principal investigator should open the opaque envelopes in an emergency.

The 0.01% atropine eyedrop and placebo eyedrop were prepared in a manner that appeared similar in appearance. The manufacturer of the eyedrop labeled the investigational eyedrop according to the randomization code number. Then, the manufacturer delivered the pre-randomized eyedrop to each recruitment center. The masked investigator was responsible for the ophthalmic measurements but was not allowed to handle the eyedrops throughout the study. During the clinical trials, neither the participants nor the masked investigator were aware of the group allocation. The masked clinical research coordinator (CRC) guided the participants in performing and finishing each of the examinations. All outcome assessments were performed by masked investigator.

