### Primary outcome

The primary outcome was to determine whether the combination of OK lens and 0.01% atropine intervention are superior to OK lens, in terms of preventing myopia progression, by evaluating the axial length elongation in these two groups of participants. For the primary outcome analysis, the myopia progression over 2 years would be determined by the difference in axial length between the baseline and 24-month visit. Other measurements obtained at the follow-up visits were considered as secondary outcome measures.

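### The primary ANCOVA names centre as its only adjustment; adding baseline age and baseline axial length would probably gain some precision at almost no cost

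*Protocol article*

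**What the plan says.** The Primary outcome section of the protocol article defines the endpoint as a change score: "the myopia progression over 2 years would be determined by the difference in axial length between the baseline and 24-month visit". The Statistics analysis section gives the model: "ANCOVA model with center effect correction was used to compare the difference of change from baseline between two groups", with a 95% confidence interval. Centre is the only term named besides treatment. The next sentence covers the other efficacy outcomes and lists no adjustment terms: "For the secondary efficacy outcomes, ANCOVA models were used to compare the difference of change from baseline between two groups".

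Three other statements bear on the choice of covariates:

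- Randomization and masking: "The randomization was stratified by center with fixed block size of 4". Centre is the only stratification factor.
- Inclusion criteria: "The participants were within 8–12 years old". Age must therefore be known for every child.
- Background: "children who develop myopia at a younger age is prone to progress more quickly". This concerns age at onset, and no correlation is given.

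The sample size was set without covariates: "The two-sample *t* test for superior statistical analysis was used for the sample size calculation".

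**The concern.** A model with treatment and centre alone is a two-way analysis of variance. The name ANCOVA calls for a continuous covariate, and none is given. If the sentence is taken at face value, any variation in elongation that age or baseline axial length could explain stays in the residual. The confidence interval for the treatment difference is then wider than it needs to be.

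Age is the better supported candidate, because the protocol's own background treats earlier onset as a marker of faster progression, and age at enrolment is a reasonable proxy for it. Baseline axial length helps only so far as it predicts change, since subtracting it has already removed the main differences in eye size between children. At stake are a few points of power and a somewhat tighter interval. The validity of the comparison is not in question.

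**Working it through.** **Inputs from the Sample size calculation section.** Mean elongation 0.09 mm (SD 0.12) with the combination and 0.19 mm (SD 0.15) with the OK lens, both at 1 year, so the difference is 0.10 mm. The design settings are "a significance level of 0.05, 95% confidence interval, 80% power, and 1:1 allocation", two-sided, with 20% loss and 96 children in total (48 per arm).

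**The plan's own figure.** The root-mean-square SD is √((0.12² + 0.15²)/2) = 0.1358 mm. The two-sample t test then needs 30 per arm for 80% power. After loss, 30/0.80 = 37.5, so 38 per arm and 76 in total. The stated 96 is not reproduced. With SD 0.15 in both arms the t test needs 37 per arm; 37/0.80 = 46.25, so 47 per arm and 94 in total, which is close. Both SDs are carried below. Why 96 does not reproduce is a separate question, but 96 is more than the stated inputs require.

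**Unadjusted power.** Evaluable children: 48 × 0.80 = 38.4, taken as 38 per arm. The standard error is SD × √(2/38):

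- SD 0.1358: SE 0.0312 mm; 0.10/0.0312 = 3.21; power 88.6%.
- SD 0.15: SE 0.0344 mm; 0.10/0.0344 = 2.91; power 81.8%.

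**Effect of covariates.** Let R² be the share of within-arm variance in change explained by age and baseline axial length together. The documents give no value, so R² is an assumption. The residual SD is SD × √(1 − R²). Estimating two extra slopes inflates the SE by about √(1 + 2/(76 − 4 − 2 − 1)) = √(1 + 2/69) = 1.0144. The net SE ratio is therefore √(1 − R²) × 1.0144.

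| R² (assumed) | Net SE ratio | Net power, SD 0.1358 | Net power, SD 0.15 |
|---|---|---|---|
| no covariates | 1.000 | 88.6% | 81.8% |
| 0.04 | 0.994 | 89.0% | 82.2% |
| 0.1 | 0.962 | 90.8% | 84.6% |
| 0.2 | 0.907 | 93.7% | 88.5% |
| 0.3 | 0.849 | 96.2% | 92.2% |

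Powers come from the noncentral t distribution, with 70 residual degrees of freedom for the adjusted rows (76 children less treatment, centre and two covariates: 76 − 6). The break-even point, where the ratio equals 1, is R² = 1 − 1/1.0144² ≈ 0.028.

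The gain is about 2 to 3 points at R² 0.1, 5 to 7 at 0.2 and 8 to 10 at 0.3, and under half a point at 0.04.

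**The case against.** The strongest reply is that the article is a condensed account and does not say that baseline axial length or age is excluded. ANCOVA of a change from baseline often implies the baseline value as covariate, and a full covariate list is commonly left to the full protocol or the SAP, neither of which is shown. This stands in part: omission is an inference from the wording. But the sentence does name one adjustment, so a reader may take the list as complete, and the model as stated can be improved.

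Three stronger readings are tempting, and the documents support none of them.

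- A reader might infer that the centre-only analysis is wrong, or biased by a chance imbalance in age. It is not. Randomisation balances age in expectation, and the interval and the type I error rate already allow for chance imbalance.
- A reader might infer that the secondary models deliberately ignore the stratification factor. The text is only silent on their terms, and a condensed article may be silent there.
- A reader might take the 2-year difference of 0.11 mm in the Background (0.29 against 0.40 mm), add an SD of 0.22 mm, and conclude that covariates lift power from 58% to 73%. That SD is nowhere in the documents. Whether 1-year inputs are adequate for a 24-month endpoint is a separate sample size question and lends no weight here.

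It is also fair to say that the background statement concerns age at onset, not age at enrolment, and that nothing in the documents shows baseline axial length predicting change. The R² range is therefore an assumption, and the gain could be negligible.

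**Conclusion.** The point holds as an efficiency and clarity improvement. The stated primary model is valid, and on the protocol's own inputs its power with 38 evaluable children per arm is already at least 80%. Adding age and baseline axial length would raise it by roughly 2 to 10 points if they explain 10% to 30% of the variance in change, and by almost nothing if they explain about 4% or less. Below about 3% they would cost a trace of precision.

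These figures assume the 1-year difference and SDs in the sample size section, 20% loss, equal slopes in the two arms, and an R² that the documents do not supply. The modest downside and the possible gain together favour adding the covariates, provided they are fixed in advance.

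**What to change.** Before unmasking, state that the primary ANCOVA of 24-month axial length change includes treatment, centre, age at baseline (continuous) and baseline axial length. For consistency, state that each secondary ANCOVA includes treatment, centre, age and the baseline value of that outcome: axial length for the 1-year comparison, and pupil size or refraction for those outcomes. If the full protocol or SAP already lists these terms, it is enough to confirm that and align the published wording.

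The cost is one sentence and two degrees of freedom in the primary model. No new data are needed. The timing matters, because covariates chosen after unmasking would be open to the charge of selection.
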